## Abstract

**Background:**

The clinical benefits of bioimpedance spectroscopy (BIS)-guided fluid management in patients on hemodialysis have been widely demonstrated. However, no previous reports have evaluated the effect of regular and serial BIS-guided fluid management on the residual renal function (RRF) in patients on peritoneal dialysis (PD). Therefore, we will evaluate the clinical efficacy of BIS-guided fluid management for preserving RRF and protecting cardiovascular events in patients on PD.

**Methods/design:**

This is a multicenter, prospective, randomized controlled trial. A total of 138 participants on PD will be enrolled and randomly assigned to receive either BIS-guided fluid management or fluid management based only on the clinical information for 1 year. The primary outcome is the change in the glomerular filtration rate (GFR) between months 0 and 12 after starting treatment. The secondary outcomes will include GFR at month 12, time to the anuric state (urine volume <100 ml/day), and fatal and nonfatal cardiovascular events during treatment.

**Discussion:**

This is the first clinical trial to investigate the effect of BIS-guided fluid management on RRF and for protecting against cardiovascular events in patients on PD.

**Trial registration:**

Clinical Trials.gov number NCT01887262, June 24, 2013.

## Background

Overhydration (OH) is common, and is associated with cardiac dysfunction and mortality in patients on peritoneal dialysis (PD)
[1, 2]. By contrast, volume depletion is associated with a more rapid loss of residual renal function (RRF) in patients on PD
[3]. Therefore, euvolemia is one of the prime objectives in these patients.

In clinical practice, the volume status is indirectly assessed using various clinical data, including edema, weight gain, and hypertension
[4]. Although there is a linear relationship between blood pressure (BP) and tissue hydration, a substantial proportion of patients do not follow that pattern. A number of patients who are euvolemic or underhydrated have systolic hypertension. Volume reduction to control systolic hypertension may result in dehydration in these patients, which may decrease RRF or compromise coronary artery perfusion, and may result in acute myocardial infarction
[5]. Conversely, patients with congestive heart failure may have a low or normal BP despite OH. Therefore, BP cannot reflect changes in the hydration status
[2].

Bioimpedance spectroscopy (BIS) has been used to measure the water compartment of the body
[6]. In patients on dialysis, body composition, including extracellular water (ECW) and intracellular water (ICW), muscle mass, and fat mass, changes slowly over several months. Regular monitoring of body composition using BIS can facilitate the optimal management of fluid balance in patients on dialysis.

The purpose of the present study is to evaluate the clinical usefulness of BIS-guided fluid management for preserving RRF and protecting against cardiovascular events in patients on PD.

## Methods/design

### Hypothesis

BIS-guided fluid management will preserve RRF in patients on PD better than fluid management guided by clinical information alone, such as BP, body weight (BWT), and physical examination results.

### Study design

The study is a multicenter, prospective, parallel-group, open-label, randomized controlled trial. It is an investigator-initiated clinical trial. The study algorithm is depicted in Figure 
1. After enrollment, clinical follow-up will be performed after 0, 2, 4, 6, 8, 10, and 12 months of treatment.

**Figure 1 Fig1:**
[figure not shown]
**Study algorithm.** BCM, body composition monitoring.

### Study participants and measurements

All patients will be selected from the outpatient renal clinic of five tertiary hospitals in Korea (Seoul National University Bundang Hospital, Seoul National University Hospital, Seoul National University Boramae Medical Center, Gachon University Gil Hospital, and Wonju Severance Christian Hospital). Patients aged 20 to 75 years who are on PD and have a daily urine output of more than 500 ml will be screened
[7]. The following tasks will be conducted at the initial visit: 1) completion of questionnaire on medical and drug history, including the use of anti-hypertensive medication and diuretics; 2) physical examination of all body systems; 3) measurement of height and weight with an empty abdomen; and 4) BP and pulse rate measurement. Participants who meet all of the inclusion and exclusion criteria and who provide written informed consent will be eligible for this study.

### Inclusion and exclusion criteria

Inclusion criteria were: age between 20 and 75 years; duration of PD (automated peritoneal dialysis (APD) or continuous ambulatory peritoneal dialysis (CAPD)) >4 weeks; daily urine output >500 ml; and provision of written informed consent.

Exclusion criteria were: contraindication to bioimpedance measurement (amputation, presence of pacemaker, defibrillator, prosthesis, or metal implants); probable discontinuation of PD or receipt of kidney transplant within 1 year; hypoalbuminemia (serum albumin <3.3 g/dl); severe heart failure (New York Heart Association Functional Classification (NYHA FC) III or IV); combined dialysis modality (PD + intermittent hemodialysis (HD)); pregnancy, lactation; enrollment in other clinical trials within 1 month; uncontrolled hypertension (>160/100 mmHg with more than three anti-hypertensive medications); cardiovascular diseases (cerebral infarction, hemorrhagic infarction, acute myocardial infarction, or unstable angina) and acute infection (pneumonia, peritonitis) within 3 months prior to the trial.

Serum and urine creatinine (Cr) will be measured by the isotope dilution mass spectrometry-traceable method using a TBA 200FR Analyzer (Toshiba, Tokyo, Japan). GFR will be calculated as the average Cr and urea clearance, which is measured by urine collection
[8].

### Randomization

The randomization process will be conducted using a web-based computer program. A list of random numbers will be generated by a computerized random allocation system operated by the Medical Statistics Support Team in Seoul National University Hospital. Eligible participants will be randomly assigned 1:1 to either the control group (fluid management based on the clinical information alone) or treatment group (BIS-guided fluid management along with clinical information). Randomization will be stratified based on the institution and presence of diabetes mellitus, and will utilize a randomized block design.

### Outcome measures

The primary outcome is the change in GFR between months 0 and 12 after starting treatment. The secondary outcomes will include GFR measured by urine collection, calculated by the mean of the Cr and urea clearance at month 12; time to the anuric state (urine volume <100 ml/day); and fatal and nonfatal cardiovascular events, including acute myocardial infarction, stroke, unstable angina, and cardiovascular revascularization. Parameters obtained by echocardiographic measurements, such as the left ventricular mass index, E/e′ ratio, left ventricular end-diastolic pressure, left ventricular ejection fraction, left atrial volume index, and BP at month 12; parameters measured by BIS, such as the OH value, ECW, and ECW/ICW; hospitalization, cardiovascular and all-cause mortality, and transfer to HD over the course of 1 year; pulse wave velocity (PWV), type and number of PD fluid and diuretics at month 12, and laboratory findings including high-sensitivity C-reactive protein (hs-CRP), N-terminal prohormone of brain natriuretic peptide, and cardiac troponin T, will also be evaluated as tertiary outcomes.

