**Table 1 Tab1:** **Data collection schedule of the COMPASS study**

Parameter	Visit time (months)							
	-1	0	2	4	6	8	10	12
Demographic information	X							
Charlson Comorbidity Index	X							
Physical examination^1^	X	X	X	X	X	X	X	X
Medication review^2^	X	X	X	X	X	X	X	X
Routine laboratory data^3^		X	X	X	X	X	X	X
Special laboratory data^4^		X						X
RRF, urine volume		X						X
Compliance		X	X	X	X	X	X	X
New events^5^		X	X	X	X	X	X	X
BCM measurement								
Treatment group		X	X	X	X	X	X	X
Control group		X						X
Kt/V		X						X
Peritoneal equilibration test		X						
PWV		X						X
Echocardiography		X						X
PD solution, medication change		X	X	X	X	X	X	X

BCM*,* Body composition monitoring; COMPASS*,* Control Of fluid balance guided by body composition Monitoring in patients on PeritoneAl dialySiS trial; Kt/V*,* Calculated using single pool equation; PD*,* Peritoneal dialysis; PWV*,* Pulse wave velocity; RRF*,* Residual renal function.

^1^Includes body weight with an empty abdomen, blood pressure, pulse rate, and edema.

^2^Number of anti-hypertensive medications and diuretics and the type of PD solution.

^3^Complete blood count, electrolyte, serum creatinine, protein, albumin, calcium, phosphorous, and fasting glucose.

^4^Total cholesterol, triglyceride, low-density lipoprotein cholesterol, high-sensitivity C-reactive protein, hemoglobin A1C, intact parathyroid hormone, N-terminal prohormone of brain natriuretic peptide, and cardiac troponin T.

^5^Any new clinical event, including hospitalization and peritonitis, will be recorded during the study period.

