### Sample size calculations

No previous report has evaluated the effect of BIS-guided fluid management on RRF in patients on PD. We therefore referred to a study showing that GFR changes over 1 year in a conventional PD solution treatment group and in a biocompatible PD solution treatment group were -16.8 ± 19.9 and 0.09 ± 40.9 l/week/1.73 m^2^, respectively
[13]. We adjusted the sample size for an estimated drop-out rate of 20% due to poor compliance, a two-sided level of significance of α = 5%, and a power of 80%, and found that 69 participants will be required in each group to find a significant difference using Student’s *t*-test. A total of 138 participants will be included in the analysis.

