### Statistical analyses

The statistical analyses will be conducted both on a per-protocol (PP) and an intention-to treat (ITT) basis. For PP analysis, all participants who complete the study will be included to evaluate the primary and secondary outcomes. For the ITT analysis, all participants who are enrolled and randomized to one of the two groups and who complete the first visit will be included.

Basic statistics will be reported in terms of mean ± SD for continuous variables, or as percentages for categorical variables. Differences between groups will be analyzed using Student’s *t*-test for continuous variables and the *χ*^2^ test or Fisher’s exact test for categorical variables. The difference in GFR between month 0 and month 12 will be compared between the two groups using Student’s *t*-test for the primary outcome. Analysis of covariance (ANCOVA) will be used to analyze the primary outcome as the secondary analysis to adjust the baseline value. Multivariate Cox proportional hazard regression models will be used to analyze the time to development of anuria. Although the institutions are mainly located in large cities, thereby limiting the likelihood of any important cluster effect, we will be sure to accommodate possible clustering in our models and analysis as required. A value of *P* < 0.05 will be considered statistically significant. All analyses will be performed using SPSS Statistics software (v21.0; IBM Corporation, Armonk, NY, USA).

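### Month-12 GFR carries the same treatment effect as the primary change in GFR, but by the plan's general rule it is tested without baseline adjustment

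*Protocol article*

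**What the plan says.** - Outcome measures defines the primary: "The primary outcome is the change in GFR between months 0 and 12 after starting treatment". The first item of the next sentence is the level at the later time point: "The secondary outcomes will include GFR measured by urine collection, calculated by the mean of the Cr and urea clearance at month 12". The abstract repeats it: "The secondary outcomes will include GFR at month 12".
- Inclusion and exclusion criteria gives one definition of GFR, which serves both outcomes: "GFR will be calculated as the average Cr and urea clearance, which is measured by urine collection".
- Table 1 schedules the row "RRF, urine volume" at months 0 and 12 only, so both outcomes rest on the same month-12 collection.
- Statistical analyses assigns Student's t-test to the primary and, as a general rule, to between-group comparisons of continuous variables. Baseline adjustment is mentioned once: "Analysis of covariance (ANCOVA) will be used to analyze the primary outcome as the secondary analysis to adjust the baseline value". No other test is named for month-12 GFR. The significance threshold is P < 0.05 throughout.
- Sample size calculations bases the design on changes in the two reference arms that "were -16.8 ± 19.9 and 0.09 ± 40.9 l/week/1.73 m^2^, respectively".

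**The concern.** Change in GFR and GFR at month 12 are listed as two outcomes of different rank, but they estimate one treatment effect. Among participants with both measurements, the two unadjusted estimates differ by exactly the observed baseline difference between arms, whose expectation under randomisation is zero.

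Two things are at stake:

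- **Interpretation.** A significant result on both could be taken as a second outcome supporting the first. A significant result on one only could be taken as the secondary failing to support the primary, or the reverse. Neither reading is sound when the effect is the same and the month-12 data are shared.
- **Precision.** Baseline GFR is measured in every participant under the schedule. An unadjusted test of month-12 GFR leaves that information unused, although the plan already uses it in the ANCOVA of the primary.

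**Working it through.** **1. Same expected difference.** Let B be GFR at month 0 and Y be GFR at month 12. The change estimate is (mean Y, treatment − mean Y, control) − (mean B, treatment − mean B, control). With 1:1 randomisation the second bracket has expectation zero, so the expected difference is the same for Y − B and for Y.

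**2. Same ANCOVA.** The model Y = a + τ·arm + β·B can be rewritten as Y − B = a + τ·arm + (β − 1)·B. Only the coefficient of B changes. The estimate of τ, its standard error and its P value are identical. The planned ANCOVA of change is therefore already the baseline-adjusted analysis of month-12 GFR.

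**3. The plan's sample size.** From Sample size calculations:

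- difference: 0.09 − (−16.8) = 16.89
- common SD: √[(19.9² + 40.9²)/2] = √1034.41 = 32.16
- n per arm for two-sided 5% and 80% power: 2 × (1.960 + 0.842)² × 32.16² / 16.89² = 56.9, so 57
- with 20% added: 57 × 1.2 = 68.4, so 69, the stated figure

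The check below uses 57 completers per arm.

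**4. What the article does not give.** There is no baseline SD of GFR and no month-0/month-12 correlation ρ. I assumed equal SD s at both times, fixed the SD of change at 32.16, and varied ρ from 0.3 to 0.9. Then:

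- s = 32.16 / √[2(1 − ρ)]
- residual SD after baseline adjustment = s√(1 − ρ²) = 32.16 × √[(1 + ρ)/2]
- correlation between the change estimate and the raw month-12 estimate = √[(1 − ρ)/2]

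At ρ = 0.3, s = 32.16/√1.4 = 27.2 and the correlation is √0.35 = 0.59. At ρ = 0.9, s = 32.16/√0.2 = 71.9 and the correlation is √0.05 = 0.22.

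**5. Simulation** (normal data, 57 per arm, true difference 16.89, 20,000 trials per row):

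| ρ | SD at each time | Power, change t-test | Power, raw month-12 t-test | Power, ANCOVA | Exactly one t-test significant |
|---|---|---|---|---|---|
| 0.3 | 27.2 | 79.6% | 91.2% | 93.4% | 18.6% |
| 0.5 | 32.2 | 79.1% | 79.2% | 88.8% | 23.4% |
| 0.6 | 36.0 | 79.8% | 70.3% | 87.4% | 28.5% |
| 0.7 | 41.5 | 79.7% | 58.2% | 85.3% | 36.2% |
| 0.8 | 50.9 | 79.2% | 41.9% | 82.9% | 47.9% |
| 0.9 | 71.9 | 79.0% | 23.6% | 80.4% | 61.5% |

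The mean estimated difference was about 16.9 for both outcomes in every row. Both tests significant in opposite directions occurred in about 0% of trials.

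**6. No true effect.** Exactly one t-test is significant in 7.5% to 9% of trials. The chance that at least one is significant is half the sum of the two rejection rates and the split rate. At ρ = 0.9 this is (4.9 + 4.9 + 9.0)/2 = 9.4%, against 5% for one test.

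**7. Another set of assumptions.** Keep the arms' unequal change SDs (19.9 and 40.9), take change as independent of baseline, and assume a baseline SD of 20, 30 or 40 with 55 per arm. The raw month-12 test then has power of about 65%, 51% and 40%, against about 78% for the change t-test. Splits occur in about 19%, 31% and 42% of trials. This set makes the month-12 value noisier by construction, because its variance is the sum of the baseline and change variances. It is one scenario, not a central estimate.

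**The case against.** The strongest case on the other side has five parts.

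- **Both outcomes are clearly defined, and reporting change alongside attained level is ordinary practice.** This stands. The article nowhere claims that month-12 GFR is independent confirmation. The risk lies in how results would be read.
- **The unadjusted t-test is an inference.** It comes from a general sentence on continuous variables, and an SAP that is not shown may name another model. This limits the point but does not remove it: as written, the rule covers this outcome, and ANCOVA is named for the primary alone.
- **The remedy is already planned, since the ANCOVA of change gives the same result.** This is true, and it is why the fix is small. The article does not make the connection, and its general rule still produces a separate raw test.
- **A reader might infer that month-12 GFR adds no evidence, or that its raw test is always the weaker one.** Neither is supported. The two unadjusted estimates correlate only about 0.2 to 0.6. At ρ = 0.3 the raw month-12 test is the more powerful of the two t-tests (91% against 80%), and at 0.5 they are equal. It is ANCOVA that does better than the raw test at every ρ examined.
- **Baseline differences among completers need not be chance.** Participants who move to HD, receive a transplant, transfer or die leave the study. If this differs by arm, a gap between change and level could carry information. That is a fair caution, but an unadjusted test would not identify the cause.

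**Conclusion.** The concern holds in a limited form. Month-12 GFR has the same expected treatment difference as the primary and uses the same collection, yet the stated general rule gives it an unadjusted test.

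At the design effect, that test and the change t-test split on significance in about 19% to 61% of trials for ρ between 0.3 and 0.9. Baseline adjustment raises the power of the month-12 comparison at every ρ examined, from 91% to 93% at ρ = 0.3 and from 24% to 80% at ρ = 0.9. These figures rest on the article's change means and SDs, 57 completers per arm, equal SDs at the two times and an assumed ρ.

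A reader might infer that the secondary will often contradict the primary. The documents do not support that without qualification. The split is one P value below 0.05 and the other above it, its frequency depends on a correlation that is not given, and it is under 10% when there is no effect. Nor does the point justify deleting the outcome: it is a published secondary outcome of a trial that is already recruiting, and removing it would raise a question of selective reporting.

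**What to change.** In Statistical analyses, or in the SAP:

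1. Keep GFR at month 12 as a secondary outcome.
2. Test it by ANCOVA with month-0 GFR as covariate in place of the unadjusted Student's t-test.
3. Report unadjusted month-12 means and SDs by arm descriptively, without a separate test.
4. State that this analysis gives the same treatment estimate and P value as the ANCOVA of change, and that agreement between them is not independent confirmation of the primary result.

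This does not guarantee agreement with the primary t-test on change. At ρ = 0.3, for example, powers of 93.4% and 79.6% imply that the two differ in at least 93.4 − 79.6 = 13.8% of trials. That difference already exists between the plan's primary and secondary analyses of change, and it would no longer appear under a second outcome name.

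The cost is wording only. Baseline GFR is already collected, so no visit, measurement or participant is added, and the primary test and the sample size stay as they are.

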### Assessment of the fluid status

For participants in the control group, clinical information obtained by physician physical examination is the standard of judgment. Clinical information is composed of four items, including measured BWT within 2 kg of the dry weight, BP less than 140/90 mmHg, absence of symptoms and signs for hypervolemia (dyspnea, edema, and crackle) or hypovolemia (dizziness and orthostatic hypotension).

For participants in the treatment group, the OH value measured by the Body Composition Monitor (BCM) (Fresenius, Medical Care Korea, Seoul, Korea), using an alternating current at 50 different frequencies (5–1000 kHz) combined with clinical information, represents the standard of judgment. The OH value is calculated using the BCM based on a physiologic tissue model that is composed of the individual’s normal ECW, normohydrated lean and adipose tissue. The OH value can be calculated from the difference between the normal expected ECW and the measured ECW
[9]. The BCM has been validated with isotope dilution methods against all available gold-standard methods in the healthy population and in patients on dialysis
[10–12].

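### Blood pressure, a tertiary outcome, is recorded at baseline and at six on-treatment visits in both arms, but the stated comparison is an unadjusted t-test at month 12 alone; a cheap gain in precision is left unused.

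*Protocol article*

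**What the plan says.** **Outcome.** Under Outcome measures, the article lists BP with the echocardiographic parameters, as "left atrial volume index, and BP at month 12". It belongs to the group that "will also be evaluated as tertiary outcomes".

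**Data collected.** Under Study design, "clinical follow-up will be performed after 0, 2, 4, 6, 8, 10, and 12 months of treatment". Table 1 marks the physical examination at months -1, 0, 2, 4, 6, 8, 10 and 12 in a single row for both arms. Its footnote 1 defines that examination: "Includes body weight with an empty abdomen, blood pressure, pulse rate, and edema". BP is therefore due twice before treatment and six times on treatment for every participant.

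**Analysis.** Under Statistical analyses, "Differences between groups will be analyzed using Student’s *t*-test for continuous variables". ANCOVA is named for one outcome only: it "will be used to analyze the primary outcome as the secondary analysis to adjust the baseline value". No repeated-measures model is named.

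**Other use of BP.** Under Assessment of the fluid status, "BP less than 140/90 mmHg" is one item of the clinical information that guides fluid management.

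**The concern.** The article fixes the time point for BP and names a general test, so the objection is to a stated choice. Single BP readings vary from visit to visit. A comparison that uses one reading per participant and ignores that participant's own baseline has a wider standard error than the collected data require.

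BP is one of the items by which fluid status is judged, so readers will look at it when they ask whether guided management changed volume control over the year. The stated comparison could miss a BP difference that the recorded data would support. What is at stake is precision on a tertiary outcome, not the GFR conclusion.

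**Working it through.** The document gives no BP standard deviation, correlation, target difference or power, so there is no planned figure to reproduce. The relative loss can be bounded under stated assumptions.

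**Inputs from the document.** Six on-treatment readings (months 2 to 12); a baseline reading; one reading used (month 12); t-test without covariates.

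**Assumptions.** Equal variance at all visits; the same correlation r between any two visits, including baseline; a constant treatment effect over months 2 to 12; complete data; a single baseline reading. The range for r is 0.5 to 0.7.

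**Formulas.** Variance of the arm difference, relative to the month-12 t-test (= 1):

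- A. Month 12, baseline-adjusted: 1 - r²
- B. Six-visit mean, unadjusted: (1 + 5r)/6
- C. Six-visit mean, baseline-adjusted: (1 + 5r)/6 - r²

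| r | A | B | C | Cut from baseline alone (1 - A) | Cut from averaging, unadjusted (1 - B) | Cut from averaging, both adjusted (1 - C/A) |
|---|---|---|---|---|---|---|
| 0.5 | 0.750 | 0.583 | 0.333 | 25% | 42% | 56% |
| 0.6 | 0.640 | 0.667 | 0.307 | 36% | 33% | 52% |
| 0.7 | 0.510 | 0.750 | 0.260 | 49% | 25% | 49% |

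The two sources of gain run in opposite directions. As r rises, baseline adjustment gains more and unadjusted averaging gains less. Unadjusted averaging reaches a 50% cut only when (1 + 5r)/6 ≤ 0.5, that is, r ≤ 0.40. With adjustment on both sides the limit is r ≤ 0.667.

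**Gradual effect.** Suppose one third of the effect is present at month 2, two thirds at month 4, and all of it from month 6. The mean effect is then (1/3 + 2/3 + 4)/6 = 0.833 of the full effect, and information is multiplied by 0.833² = 0.694. With both sides baseline-adjusted, the net gain from averaging is 1 - 0.444/0.694 = 36% at r = 0.5 and 1 - 0.510/0.694 = 27% at r = 0.7. Without baseline adjustment it is 1 - 0.583/0.694 = 16% at r = 0.5. At r = 0.7 it turns into a small loss, since 0.750/0.694 = 1.08.

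**Decaying correlation.** Let the correlation be 0.7, 0.8 or 0.9 between adjacent 2-month visits and decay geometrically.

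- Baseline to month 12 is six steps, so adjusting month 12 for baseline cuts the variance by 0.7¹² = 1%, 0.8¹² = 7% or 0.9¹² = 28%.
- Averaging without adjustment cuts it by 44%, 32% or 18%.
- Averaging with adjustment on both sides cuts it by 55%, 53% or 54%.

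Decay therefore mainly weakens the baseline step.

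**Illustration in mmHg.** Assume a systolic SD of 20 mmHg, a true difference of 6 mmHg, r = 0.5, and 55 evaluable per arm (69 × 0.80 = 55.2). Power is Φ(difference/SE - 1.96).

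- Month-12 t-test: SE = 20 × √(2/55) = 3.81; power 35%.
- Month 12, baseline-adjusted: SE = 3.81 × √0.750 = 3.30; power 44%.
- Six-visit mean, unadjusted: SE = 3.81 × √0.583 = 2.91; power 54%.
- Six-visit mean, baseline-adjusted: SE = 3.81 × √0.333 = 2.20; power 78%, or 62% with the gradual effect (6 × 0.833 = 5 mmHg).

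**The case against.** **A different target.** Average BP over months 2 to 12 is not the month-12 value. Month 12 is a coherent choice, because GFR, echocardiography, pulse wave velocity and the control arm's final body composition measurement are all read then. Early BP also covers the period in which treatment is being adjusted. With complete data, a model with arm-by-visit terms adds little to the month-12 contrast beyond baseline adjustment. This stands, and it is why the month-12 contrast should stay as the outcome.

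**A low tier.** BP is tertiary and the trial is not sized on it. This stands and limits the priority.

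**A condensed article.** The general t-test sentence does not mention BP, and a fuller document could add a model. That is possible. The time point and the general test are nevertheless stated, and covariate adjustment is named only for the primary outcome.

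**Stronger readings that the documents do not support.**

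- A reader might infer that at least half the information is lost. Against the unadjusted t-test, the baseline-adjusted six-visit mean does cut variance by 67% to 74% at r = 0.5 to 0.7 (1 - C), but that merges the gain from the baseline covariate with the gain from the five extra readings. The readings alone give 42% to 25%.
- A reader might infer that the interim readings are thrown away. They are used in care; they are absent only from the stated outcome comparison.
- A reader might infer that anyone who leaves before month 12 contributes nothing. The article does not describe how missing BP is handled, and its intention-to-treat set includes everyone randomized who completes the first visit.
- A reader might take BP to be the only outcome followed repeatedly and equally in both arms. Table 1 also schedules review of diuretics and PD solution type at every visit, and hospitalization is recorded throughout.

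**Conclusion.** The point holds as a minor inefficiency. The stated BP comparison leaves out the baseline readings and five of the six on-treatment readings, although all are scheduled in both arms. Under equal correlation of 0.5 to 0.7 and a constant effect, the unused variance reduction is 25% to 49% from baseline adjustment of month 12 alone. Moving to the six-visit mean saves 42% to 25% unadjusted, or 56% to 49% with baseline adjustment on both sides. These figures rest on assumed correlations, because the document gives none. A gradual effect reduces the gain from averaging and can remove it when there is no baseline adjustment; decaying correlation mainly reduces the gain from the baseline covariate. The t-test is valid as stated, only less precise than it could be, and nothing here touches the primary GFR conclusion.

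**What to change.** Under Statistical analyses, state that systolic and diastolic BP will each be analysed by a linear mixed model for repeated measures over months 2 to 12, with arm, visit, arm-by-visit interaction, baseline BP, institution and diabetes (the last two being the stratification factors). Say in advance whether baseline is the month-0 reading or the mean of months -1 and 0. Keep the month-12 contrast from this model as the stated outcome, and report the arm difference averaged over months 2 to 12 beside it.

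The cost is wording only: no added visits or data, and SPSS, the software already named, can fit the model. The downside is small. The average answers a different question and includes early visits at which the effect may be incomplete, so it should be labelled as supplementary. With complete data, the month-12 contrast will gain mainly from the baseline covariate.
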